# Reduction of the long-term use of proton pump inhibitors by a patient-oriented electronic decision support tool (arriba-PPI): study protocol for a randomized controlled trial

**DOI:** 10.1186/s13063-019-3728-2

**Published:** 2019-11-21

**Keywords:** General practitioner, Evidence-based medicine, Computerized clinical decision support system, Deprescribing, Proton pump inhibitors

## Abstract

**Background:**

Proton pump inhibitors (PPIs) are increasingly being prescribed, although long-term use is associated with multiple side effects. Therefore, an electronic decision support tool with the aim of reducing the long-term use of PPIs in a shared decision-making process between general practitioners (GPs) and their patients has been developed. The developed tool is a module that can be added to the so-called arriba decision support tool, which is already used by GPs in Germany in routine care. In this large-scale cluster-randomized controlled trial we evaluate the effectiveness of this arriba-PPI tool.

**Methods:**

The arriba-PPI tool is an electronic decision support system that supports shared decision-making and evidence-based decisions around the long-term use of PPIs at the point of care. The tool will be evaluated in a cluster-randomized controlled trial involving 210 GP practices and 3150 patients in Germany. GP practices will be asked to recruit 20 patients aged ≥ 18 years regularly taking PPIs for ≥ 6 months. After completion of patient recruitment, each GP practice with enrolled patients will be cluster-randomized. Intervention GP practices will get access to the software arriba-PPI, whereas control GPs will treat their patients as usual. After an observation period of six months, GP practices will be compared regarding the reduction of cumulated defined daily doses of PPI prescriptions per patient.

**Discussion:**

Our principal hypothesis is that the application of the arriba-PPI tool can reduce PPI prescribing in primary care by at least 15% compared to conventional strategies used by GPs. A positive result implies the implementation of the arriba-PPI tool in routine care.

**Trial registration:**

German Clinical Trials Register, DRKS00016364. Registered on 31 January 2019.

## Background

Prescriptions of proton pump inhibitors (PPIs) have been increasing considerably in recent years in many countries. According to the German drug prescription report, a total of 3.7 billion defined daily doses (DDD) of PPIs were prescribed in Germany in 2015. Thus, PPIs are one of the most commonly prescribed drugs [1]. Even though the number of PPI prescriptions slightly decreased from 2016 to 2017, the number of prescribed PPIs still remains high. The halt of the rising trend might be due to the recent discussion around possible side effects caused by PPIs when used for long periods [2].

Positive evidence exists regarding the effectiveness of PPIs in the treatment of gastrointestinal ulcers [3], eradication therapy [4], reflux disease [5], and gastric pre-malignant lesions [6]. However, PPIs are also increasingly used as a means of protecting the stomach in polypharmacy patients (i.e. the current intake of several drugs [7]) and in combination with non-steroidal antirheumatic drugs or platelet aggregation inhibitors. Furthermore, they are used in patients suffering from nun-ulcer dyspepsia and for stress ulcer prophylaxis during hospital stay [1, 8]. PPIs should be used for short periods and only few indications justify their long-term use. Even though long-term use without indication is considered inappropriate [9], PPIs are frequently overused as lifestyle drugs [10]. Long-term use of PPIs poses potential risks [9], such as interactions with other drugs or side-effects [11–13]. Once prescribed, withdrawing PPIs seems to be difficult due to a potential rebound effect reactivating dyspeptic complaints [14]. Apart from the potential risks, the frequent use of PPIs contributes to substantial costs for the healthcare system [1].

Given the frequent use and overuse of PPIs, withdrawing PPIs is important and supporting strategies for GPs are needed [15]. Deprescribing is “the process of withdrawal of an inappropriate medication, supervised by a health care professional [ …]” [16]. A recent Cochrane review identified the benefits and harms of deprescribing for chronic PPI use. Six studies were included; five of them deprescribed PPIs on-demand, whereas one abruptly discontinued PPIs. Overall, a significant reduction in the number of PPIs taken could be achieved. The deprescribing of PPIs led to side effects such as significantly more gastrointestinal complaints [17]. However, a recently developed guideline to support deprescribing of PPIs concluded that PPIs can be withdrawn without causing any major clinical harm [15]. Still, there are not enough data on the long-term benefits or harms of PPI withdrawal and the cost/resource use of the interventions is not known. Furthermore, the patient was not involved in the deprescribing process [17].

Involving the patient into the deprescribing process is important and it has been shown that deprescribing interventions are most effective when they involve the patient [18]. Furthermore, decision aids can support patients in their treatment decisions, enhance informed, value-based choices, and improve patient–practitioner communication compared to usual care [19].

The electronic decision support tool arriba is widely used in Germany and has been originally developed to support shared decision-making (SDM) processes in GP practices in the prevention of cardiovascular diseases. Arriba was developed by Institutes of General Practice of several German universities and is nowadays managed by the independent and non-profit arriba cooperative society. It is based on the principles of evidence-based and individual patient-oriented medicine [20]. Today, arriba consists of several modules that have been scientifically evaluated previously [20–25].

Given the long-term overuse of PPIs and their potential risks, there is a strong need for effective interventions optimizing the long-term use of PPIs. Therefore, an additional module for the arriba tool has been developed. The arriba-PPI tool is targeted at the primary care setting to support GPs to identify and reduce inappropriate long-term prescribing of PPIs in a SDM process with their patients. It presents options and their evidence base in an easy to understand way and offers practical behavioral advice and individualized messages for patients. In line with the MRC framework for complex interventions [26], we evaluated the arriba-PPI tool in a feasibility study before the start of this trial [27].

## Methods/Design

We followed the Standard Protocol Items: Recommendations for Interventional trials (SPIRIT checklist) in designing the study protocol (see Additional file 1). As recommended by the MRC framework [26], our project incorporates three of the four elements: development; piloting; and evaluation. Upon positive evaluation, the arriba-PPI tool will be implemented (fourth element of the MRC framework). This study protocol mainly focuses on the evaluation.

### Objectives of the study

Our principal hypothesis is that a patient-oriented strategy of medication reduction using the arriba-PPI tool in primary care practices reduces PPI prescriptions by at least 15% in comparison to conventional consultations over a period of six months (see Table 1).

**Table 1 Tab1:** PICO research question of the arriba-PPI trial

PICO-Item	Research question
P (patient)	Patients aged ≥ 18 years regularly using PPIs over ≥ 6 months in primary care
I (intervention)	GPs of enrolled patients with access to the arriba-PPI tool
C (comparison)	GPs of enrolled patients without access to the arriba-PPI tool providing care as usual
O (outcome)	Cumulated defined daily doses of PPI per study patient after 6 months

Our secondary objective is to evaluate the effectiveness of the implementation of the arriba-PPI tool in our extension study (6–12 months).

Furthermore, we aim to describe the GPs’ and the patients’ experiences in using the arriba-PPI tool within a primary care consultation in two sub-studies.

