### Sample size calculation

We based our sample size calculation on our primary endpoint. According to data of the statutory health insurance AOK Hessen, the average DDD of all PPI prescriptions per GP practice (averaged across all GP practices) accounts to 8244.47 per quarter with a standard deviation of 7850.89 (variation coefficient 0.95). This value is based on an average number of patients with PPI prescriptions of 56.20 per GP practice. Therefore, an average of DDD of PPIs of 146.7 per patient is assumed (8244.47/56.2). Taking into account a variation coefficient of 0.95, the standard deviation is 139.7 DDD of PPIs on a patient level. We consider a reduction by 15% as relevant, which would correspond to a difference of 22 DDD (15% of 146.7) between the control and intervention groups at T1. According to the sample size calculator for cluster-randomized trials of the University of Aberdeen’s Health Services Research Unit [29], we will need 204 GP practices with 15 patients each if we want to prove such a difference with an intraclass correlation coefficient of 0.1 [30], a significance level of 0.05, and a power of 80%. The primary outcome relates to patient-level data. Thus, we adapted our calculation to the cluster structure (patients in GP practices). The number of practices refers to the number that needs to be randomized. To cover for drop-out practices after randomization, we increased the number of practices to be recruited to 210. In addition, patients might leave the study at their own request after inclusion in the study but before receiving the actual intervention. We decided to have a buffer considering non-predictable dropouts. Therefore, each study practice is required to recruit at least 15 patients but not more than 25 patients, as differences in cluster size can have a negative influence on intracluster variability. Practices will include patients in the study according to the chronological order in which the patients signaled their willingness to participate in the study. By setting this range of patients, the probability that the number of patients per practice varies only minimally increases. If 15 potential study patients cannot be enrolled in the study within the timeframe for recruitment, the study practice and its recruited study patients will still be included in the analysis.

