### Data management and statistical analysis

Data will be recorded into SPSS at each study center and transferred to the blinded trial statistician. We will use intention-to-treat and per-protocol analyses. The primary outcome will be analyzed by multilevel analyses with the statistical program R following intention-to-treat principles [31]. These analyses take into account the clustering of patients by practices and allow for different modelling of predictors, e.g. group affiliation as fixed and/or random effect. Furthermore, these analyses allow adjustment for variables which showed differences between the intervention and control groups despite randomization and which are considered to be of prognostic importance. In case of missing variables, suitable imputation methods will be used [32]. We will perform sensitivity analyses (worst case, best case, complete case) in order to check for the influence of missing data on the results.

The evaluation for the secondary outcomes will also be done by multilevel analyses by adopting covariates on patient and/or cluster level. Elaborated evaluations in multivariate procedures allow a more detailed analysis of prescription behavior. All statistical tests will be two-tailed and an alpha of 5% will be used throughout. Besides statistical significance, effect sizes will also be evaluated [33].

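### The principal hypothesis claims a reduction of at least 15%, but the sample size and two-sided test fit only a test against no difference, so significance alone would not establish 15%

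*Protocol article*

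**What the plan says.** Under Objectives of the study, the principal hypothesis is that the tool "reduces PPI prescriptions by at least 15% in comparison to conventional consultations over a period of six months". The Discussion part of the abstract repeats it: the tool "can reduce PPI prescribing in primary care by at least 15% compared to conventional strategies used by GPs". The next sentence there reads "A positive result implies the implementation of the arriba-PPI tool in routine care". Methods/Design says "Upon positive evaluation, the arriba-PPI tool will be implemented", without mentioning 15%. Neither place defines a positive result or a positive evaluation.

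The Sample size calculation section gives 15% a different role. It says "We consider a reduction by 15% as relevant", converts this to "a difference of 22 DDD (15% of 146.7) between the control and intervention groups at T1", and concludes "we will need 204 GP practices with 15 patients each if we want to prove such a difference", using an intraclass correlation of 0.1, a significance level of 0.05 and 80% power.

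Under Data management and statistical analysis, the primary outcome goes into a multilevel model on intention-to-treat principles, and "All statistical tests will be two-tailed and an alpha of 5% will be used throughout". No margin or shifted null is mentioned. The sentence after that adds that effect sizes will be assessed as well as significance.

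**The concern.** A difference that a trial is powered to detect is not a difference that a significant result demonstrates. The hypothesis and the word prove treat 15% as the quantity to be shown, whereas the sample size section uses it as the alternative in a test whose null is no difference. Rejecting that null shows that the effect is not zero. It does not show that the effect is 15% or more.

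What is at stake is the conclusion that may be drawn. A significant result with an estimate below 15% could be read as confirming the principal hypothesis, because the test was passed, or as failing it, because the estimate falls short. The text does not settle which reading applies, and it is better settled before results are known.

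**Working it through.** **Inputs (Sample size calculation).** Mean 146.7 DDD per patient; SD 139.7 DDD; difference 22 DDD (15% of 146.7); intraclass correlation 0.1; 15 patients per practice; alpha 0.05; power 80%. Two-sidedness comes from the statistical analysis section. The allocation ratio is not stated; 1:1 is assumed.

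**1. Reproduce the plan's figure with a null of zero.**
- Patients per arm without clustering: 2 × (1.960 + 0.842)² × 139.7² / 22² = 633.
- Design effect: 1 + (15 − 1) × 0.1 = 2.4.
- Practices per arm: 633 × 2.4 / 15 = 101.28, rounded up to 102.
- Total: 2 × 102 = 204, as stated.

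The one-sided version gives 499 per arm, 79.84 rounded up to 80 practices per arm and 160 in total, which does not match. So 204 corresponds to a two-sided test of no difference, with 22 DDD as the alternative.

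**2. Where significance begins.**
- Each arm has 102 × 15 = 1,530 patients. SE = 139.7 × √(2 × 2.4 / 1,530) = 7.82 DDD.
- Smallest significant reduction: 1.96 × 7.82 = 15.3 DDD; 15.3 / 146.7 = 10.5%.
- With the 210 practices to be recruited, SE = 7.71 DDD, giving 15.1 DDD or 10.3%.

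**3. What an estimate of exactly 15% would show.** 22 ± 15.3 gives 6.7 to 37.3 DDD, or about 4.5% to 25.5%. This is significant, but reductions well below 15% are not excluded.

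**4. What establishing at least 15% would need.**
- The lower confidence limit must reach 22 DDD, so the observed reduction must be 22 + 15.3 = 37.3 DDD; 37.3 / 146.7 = 25.5%.
- If the true reduction is exactly 15%, power against zero is Φ(22 / 7.82 − 1.96) = 80%, but the chance that the interval lies wholly beyond 15% is Φ(−1.96) = 2.5%.
- For larger true reductions (assumed, since the document gives none above 15%), that chance is 15% at a true 20%, 47% at 25% and 80% at 30%.

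**5. Time scale.** The 146.7 DDD comes from quarterly data, while the endpoint covers six months. The percentages above depend only on the ratio of SD to mean, so they are unchanged if both scale together.

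**The case against.** Several points on the other side are sound.

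- **A hypothesis may state an expectation.** Naming at least the planning difference is a common way to describe the alternative, and the sample size section does call 15% relevant. This explains the wording but does not remove the mismatch: the claim is stated twice as the principal hypothesis and reinforced by the word prove.
- **Effect sizes will also be evaluated.** This mitigates the point, since the plan does not look at p-values alone. It does not say how the estimate or its interval will be compared with 15%.
- **An analysis plan not shown may hold formal hypotheses and success criteria.** It may, and the absence of such detail here is not the point. The hypothesis, the sample size and the test all stand in this article, and they do not agree.
- **The figures are generic.** In any two-sided 5% trial with 80% power, significance starts at 1.96 / 2.80 = 70% of the planning difference; here 0.70 × 15% = 10.5%. This is correct. The numbers show how far the claim exceeds the design; they do not mean that the trial is unusually small or badly sized.

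A reader might also infer that the plan ties roll-out to p < 0.05 alone. The documents do not support that. No passage defines a positive result as statistical significance. In the abstract the implementation sentence follows the 15% hypothesis and can equally be read as requiring 15%; Methods/Design mentions neither. The article's main Discussion also expects the qualitative work to inform future implementation.

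**Conclusion.** The point holds as a mismatch between the claim and the design. The hypothesis of a reduction of at least 15% is a property that the sample size and the two-sided test cannot deliver through significance alone: significance begins at about 10.5%, while establishing at least 15% needs an observed reduction of about 25.5%, with a chance of about 2.5% if the truth is exactly 15%.

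This rests on 1:1 allocation, 204 practices with 15 patients each, the plan's own SD and intraclass correlation, and percentages taken relative to a control mean of 146.7 DDD. The zero null is not written out; it is inferred from the plain two-tailed test and the exact reproduction of 204.

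It would be too strong to say that a significant result contradicts or cannot support the hypothesis. Such a result is compatible with 15% or more, and an interval lying wholly beyond 15% would establish it. The sample size arithmetic is correct, and a larger trial is not called for.

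**What to change.** Change the wording as follows:

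- **Objectives and abstract:** state the principal hypothesis as a reduction in six-month cumulated DDDs of PPIs compared with usual care, with a null of no difference. Describe 15% as the relevant difference that the trial has 80% power to detect.
- **Sample size calculation:** replace prove with detect.
- **Conclusions:** claim a reduction of at least 15% only if the whole confidence interval lies at or beyond 15%.
- **Implementation statement in the abstract:** say what a positive result means and how the estimate and its interval will be read against the 15% benchmark. Which threshold to adopt for implementation is the sponsor's decision; none is prescribed here.

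The cost is small: data, sample size, endpoint and model are unchanged. The downside is that a significant result will support a weaker claim than the one now stated, and the stronger claim is unlikely to be reached unless the true reduction is well above 15%.

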### Trial design and setting

The arriba-PPI trial is a national multicenter cluster-randomized controlled trial with an observation period of one year to reduce long-term prescription of PPIs. It will be conducted in Germany in the mid- and north Hessia and Westphalia-Lippe regions. Three study centers will be involved: the Institute of General Practice of Marburg University; Institute of General Practice of Heinrich-Heine-University Düsseldorf; and Institute of General Practice and Family Medicine of Witten/Herdecke University. The arriba-PPI trial will be located in the primary care setting. Details on the study procedure are outlined in Fig. 1.

**Fig. 1 Fig1:**
[figure not shown]
Course of the study

### Ethics approval

The study has been approved by the three local ethics committees (see “Declarations”).

### Recruitment of GP practices and patients

Before the recruitment of GP practices and patients, recruitment-regions will be selected. In these prespecified regions, all GPs will be informed about the study and will be invited to participate. All GP practices will obtain a written invitation (letter and/or fax) and will be followed up by phone calls. The study design will be presented at several network meetings for GPs, where the GPs will be asked to participate. Additionally, the health insurance BARMER will identify GP practices with a higher prescription rate of PPIs compared to the median prescription rate of all practices of the BAMER database. BARMER will contact these practices twice via mail and invite them to participate.

Participating GP practices will be visited by a research assistant from the study center providing detailed information about the study before patient recruitment. GP practices will then invite all consecutive patients with a PPI prescription consulting the practice to participate in the study and will inform them about the study orally and in writing. After completing recruitment, the practice will be randomized.

### Inclusion and exclusion criteria

GP practices will need to meet the following inclusion criteria to participate: German as the predominant language in patient communication; the ability to collect prescription data in an electronic health record (EHR) as a technical prerequisite; and the willingness to provide PPI prescription data collected in the EHR. Practices will be excluded if they only treat narrowly defined patient groups or provide services only (e.g. alternative or complementary treatments), do not regularly prescribe PPIs, or do not use an EHR.

Patients with a regular prescription of PPIs of ≥ 6 months will be included. We defined regular prescription as taking at least one PPI pill daily or as taking regularly several PPI pills per week (such as four pills per week/every other day). Furthermore, patients will have to be aged ≥ 18 years and give informed consent according to the declaration of Helsinki. Patients will be excluded from the study if they do not want to participate, cannot provide informed consent, or are not able to communicate in German. Only patients who have access to the practice will be included, since the arriba-PPI tool is only available for computers. Lastly, patients are excluded if their PPIs are prescribed for limited time periods or only as required.

### Randomization

The GP practice is regarded as the unit of randomization. Each participating GP practice with the recruited patients will be randomized to either having access to the arriba-PPI tool (intervention) or not and performing care as usual (control). We decided to apply cluster randomization in order to avoid contamination if the GP would use the tool for some patients but not for others as we expect that a learning effect will take place. After completion of patient recruitment, the GP practice will notify the corresponding study center providing the number of patients recruited. The practice will then be randomized using computerized sequence generation with a simple randomization scheme generated by the random package of the program R [28]. Randomization will be stratified by study center. Randomization lists will be kept closed. To assure concealment of allocation, no patients can be included once recruitment is completed and randomization has been performed.

